## Introduction

Suicide is a major public health concern, causing more than 700,000 deaths per year worldwide (1). Moreover, as suicidal behaviors prevalence increases during adolescence (2), suicide is reported to be the fourth leading cause of death among people aged 15 to 29 (1). Having a history of suicide attempts is the most important risk factor for suicide, with a recent study reporting a higher risk of suicide mortality for 6 months following a suicide attempt, with a peak mortality risk at 1 month (3). Similarly, the risk of suicide re-attempt is at its highest in the first 6 months after an index attempt, and declines over time (4). The dangerousness of the means and its lethality increase with age (5). With fewer studies focusing on adolescents and young adults, suicide re-attempts are reported to occur in this population in 12% at 3 months (6), 17% at 6 months (7), and in 25–31% at 1 year (8).

The biopsychosocial model of suicide theorizes suicidal behaviors as a result of complex trait and triggering factors including socio-demographic, clinical, and biological determinants (9). Identified individual risk factors for suicide and suicide re-attempts include: a diagnosed psychiatric disease, family history of suicide and psychiatric illness, substance abuse, impulsivity, sexual or physical abuse and bullying, active suicidal ideation, conflicts with romantic relationship, and, most importantly, a personal history of suicide attempt (10).

Regarding the biological underpinnings, most studies conducted in adults have shown that suicidal behaviors could be associated with lower baseline, chronic, and/or reactivity of cortisol levels (11–13), suggesting a failure of the hypothalamo-pituitary-adrenal (HPA) axis stress-response system. Other biological markers of interest involve proinflammatory markers such as C-Reactive Protein (CRP) and interleukin (IL)-6 (14–16), a history of exposure and seropositivity to *toxoplasma gondii* (17), and low levels of Brain-Derived Neurotrophic Factor (BDNF) (18, 19), although the evidence to support their implication is less consistent (20, 21).

These biological processes may be particularly relevant during the transition from adolescence to adulthood, a critical period of development characterized by exposure to interpersonally-themed stressors, increased impulsivity and risk-taking behaviors, and onset of severe psychiatric disorders (22).

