### Study Design

The overall study design is shown in Figure 1. According to our sample size calculation (see below), 200 adolescents and young adults will be recruited in the study. Upon enrollment, baseline data will be collected. Clinical and socio-demographic data will be investigated through the computerized clinical chart and through relatives if necessary. Psychiatric diagnoses will be established according to the Diagnostic and Statistical Manual of Mental Disorders, Fifth edition (DSM-5) during a standardized psychiatric interview. During hospitalization, participants will complete standardized and validated questionnaires. The morning after admission to the emergency unit, a first blood sample will be taken from fasting patients at 7:00 am for biological measurements. Two other blood samples will be collected and stored at −80°C for future research purposes (one EDTA sample and one PAXgene blood RNA tube). Patients who are not fasting will be rescheduled. All inpatients will benefit from usual psychiatric care and will receive appropriate referrals upon discharge. They will also be integrated into the VigilanS brief contact intervention program (23), which is currently being rolled out nationally, and has demonstrated efficacy in reducing suicide re-attempts (24).

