#### Biological Factors

The levels of CRP, orosomucoid, fibrinogen, cortisol, IL-6, and anti-toxoplasma gondii immunoglobulin G (IgG) and immunoglobulin M (IgM) will be measured in the blood as routine analyses by the central biological laboratory of the hospital.

To assess a potential imbalance between neurotrophic and proapoptotic systems (38), we will measure the proportion of mature BDNF and pro-BDNF respectively, as exploratory analyses. Plasma mature BDNF and pro-BDNF levels will be assessed by enzyme-linked immunosorbent assay (Biosensis, BEK-2211/2237) in collaboration with biologists from Hospices Civils de Lyon. As a measure of chronic stress exposure in contrast to blood cortisol analysis, we will measure hair cortisol levels. Hair strands will be cut carefully with scissors as close as possible to the scalp, and stored at room temperature in aluminum foil. Cortisol levels will be determined from the 3 cm segment of hair closest to the scalp. This represents hair growth over the 3-month period prior to sampling based on an average hair growth of 1 cm/month. In collaboration with University Hospital of Bordeaux, assays will be performed by Liquid Chromatography with tandem mass spectrometry as previously detailed in the study of Brossaud and colleagues (2021) (39).

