Impulsivity can be described as a general pattern of behavior (trait-impulsivity), as responses that are not conformed to their context (action-impulsivity), or as inability to delay reward or to take future consequences into account (choice-impulsivity). Due to a delayed development of top-down prefrontal areas relative to subcortical regions involved in desire and fear, adolescents and young adults are particularly susceptible to impulsive behaviors (41), which suggests an increased risk of suicidal behaviors. This dimension therefore constitutes an interesting criterion for suicide re-attempt (42).

For biological measures, we will explore whether suicide re-attempt could be associated with alterations of the HPA axis, neuroplasticity, and inflammation, including a recent toxoplasmosis infection. These biological systems are highly connected since glucocorticoids dysregulation could lead to increased inflammatory activity and impaired neuroplasticity (43, 44).

Cortisol is the key hormone of the stress-response system, and failure of the HPA axis in response to stress may underlie suicidal crises (22). Most findings, conducted in the general population, suggest that both lower and higher baseline and stressor-induced cortisol levels have been associated with suicide, consistent with allostatic load theories resulting from the adaptation to the environment (22, 45). Accordingly, we will quantify blood cortisol levels as a measure of an acute stress provoked by the suicide attempt, and, in collaboration with the University Hospital of Bordeaux, we will assess hair cortisol, as a retrospective indicator of cumulative cortisol levels during the last 3 months preceding the attempt. To date, hair cortisol has been used in various settings as a reliable marker of long-term exposure to stress (46–48). A recent meta-analysis investigating the association between hair cortisol levels and depression found contradictory results (49). Nonetheless, because altered functioning of the HPA axis has been strongly involved in major depressive disorder (50), depression is a potential confounding variable of cortisol measures and will be considered in the analysis. Similarly, thyroid dysfunction may result in depressive symptoms (51). Thyroid function tests were not systematically performed in the cohort, thus we cannot rule out depression with subclinical hypothyroidism.

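### Blood cortisol is described as the acute stress caused by the attempt, but one fasting 7:00 am sample, timed from admission, cannot separate that response from the ordinary morning level

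*Protocol article*

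**What the plan says.** **What the value is meant to show.** The Discussion states: "we will quantify blood cortisol levels as a measure of an acute stress provoked by the suicide attempt". Biological Factors makes the same contrast from the other side: "As a measure of chronic stress exposure in contrast to blood cortisol analysis, we will measure hair cortisol levels". Blood is thus the acute measure and hair the chronic one.

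**How the sample is taken.** Study Design states: "The morning after admission to the emergency unit, a first blood sample will be taken from fasting patients at 7:00 am for biological measurements". It adds: "Patients who are not fasting will be rescheduled". The remaining tubes are not serial cortisol: "Two other blood samples will be collected and stored at −80°C for future research purposes". Biological Factors lists cortisol with markers that "will be measured in the blood as routine analyses by the central biological laboratory of the hospital", and describes no before-and-after or challenge measurement.

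**The article's own categories.** The Introduction summarises earlier adult work in terms of "lower baseline, chronic, and/or reactivity of cortisol levels". The Discussion likewise treats baseline and stressor-induced cortisol as separate quantities.

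**Planned analysis.** Under Secondary Outcomes, continuous variables are compared between re-attempters and the others by t-test or Mann-Whitney test, and variables with P below 0.2 go into a Cox model. The Discussion names depression as a confounder of the cortisol measures.

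**The concern.** The stated meaning of the variable and the rule for collecting it do not fit together. A response to an event is identified either by timing the sample from the event or by comparing it with a second value from the same person. Neither is described. The draw is fixed by clock hour and by admission, so the time since the attempt differs between patients and has no stated upper limit.

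What is at stake is interpretation. The Discussion motivates cortisol by a failure of the HPA axis in response to stress. With the present wording, a null result could be reported as evidence against a link between the acute stress response and re-attempt, and a positive one as a reactivity finding. The sample supports neither statement. It does support a statement about the morning level.

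**Working it through.** The plan gives no figure to reproduce here. The check has three parts.

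**1. Delay from admission to draw.** Inputs: 7:00 am, the morning after admission (Study Design). Assumption: this means the next calendar day. For admission at clock hour h, delay = (24 − h) + 7 = 31 − h hours, plus 24 hours for each day of rescheduling.

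| Admitted at | First morning | One day later | Two days later |
|---|---|---|---|
| just after 00:00 | 31 h | 55 h | 79 h |
| 06:00 | 25 h | 49 h | 73 h |
| 12:00 | 19 h | 43 h | 67 h |
| 18:00 | 13 h | 37 h | 61 h |
| just before 24:00 | 7 h | 31 h | 55 h |

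The time from attempt to admission is not given and adds to every cell.

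**2. How much of an attempt-induced rise could remain.** The article gives no decay rate, so this is a range under assumptions: admissions spread evenly over the day, a rise that starts to decay at admission, and a half-life H of 1 to 6 hours. With k = ln 2 / H:

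- mean share left = (e^(−7k) − e^(−31k)) / (24k)
- SD of the share = square root of [(e^(−14k) − e^(−62k)) / (48k) − mean²]

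| H | Mean share left | SD between patients |
|---|---|---|
| 1 h | 0.05% | 0.0013 |
| 1.5 h | 0.4% | 0.0076 |
| 3 h | 3.6% | 0.048 |
| 6 h | 15% | 0.114 |

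At H = 6 h the share runs from e^(−7k) = 45% down to e^(−31k) = 3% through delay alone. After one rescheduled day its mean is 0.9%. So under these assumptions most of the rise has gone in the average patient, and what remains depends on arrival time.

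**3. Does the varying delay damage the comparison?** Inputs: n = 200 and 12.4% re-attempts (Sample Size Calculation), so 200 × 0.124 = 24.8, about 25 against 175. Assumption: a true group difference of 0.6 biological SD. If the attempt-induced rise is R biological SDs, delay adds variance (0.114R)², and the standardised difference becomes 0.6 / √(1 + (0.114R)²). At H = 6 h, the half-life that leaves the most noise, a two-sided t-test at 0.05 (noncentral t) gives:

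| R | Standardised difference | Power |
|---|---|---|
| 0 | 0.600 | 80% |
| 1 | 0.596 | 79% |
| 2 | 0.585 | 78% |
| 3 | 0.568 | 75% |

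Letting the number of events vary at random (simulation) gives about 79% without delay noise and 74% to 78% for R from 3 down to 1. For delay noise to equal one biological SD, R would have to be 1 / 0.114, about 8.8, at H = 6 h; about 21 at 3 h; and about 787 at 1 h.

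**The case against.** The strongest reply is that *acute* serves mainly to contrast blood with hair. No hypothesis, outcome or test concerns reactivity: the Abstract lists cortisol levels, and the Introduction speaks of HPA axis activity. The planned comparison is one of levels, and clock hour and fasting state are already standardised. All of this is right, and it limits the weight of the point. It does not remove it, because the Discussion goes beyond *acute* and attributes the stress to the attempt, which the sampling cannot show.

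Two stronger readings are tempting, and the documents support neither.

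- *That the sample measures basal cortisol.* The fixed hour and fasting suggest it, but nothing in the article calls it basal. Patients are in a psychiatric crisis unit after an attempt, and residual or continuing stress may contribute. The decay model above treats the stress as a single impulse, which the article does not say.
- *That uneven delay seriously weakens the comparison.* Extra noise of one biological SD would bring power for a 0.6 SD difference down to about 50%, but delay would produce that much noise only with a rise of about 8.8 SD or more. For rises of 1 to 3 SD the loss is a few points.

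It is also fair to say that covariates and the handling of rescheduled samples commonly belong in an analysis plan, which is not shown. Their absence from the article is therefore no fault. They appear below only as a check that supports the narrower wording.

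**Conclusion.** The point holds as a minor mismatch between a stated construct and the sampling rule. The blood value cannot separate a response to the attempt from the ordinary morning level, because there is one value and its timing follows admission and the clock.

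This rests on the text alone. The delay of 7 to 31 hours rests on the next-calendar-day reading. The residual shares of 0.05% to 15% and the power figures rest on an assumed decay and an assumed effect, and the conclusion does not depend on them.

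The primary outcome is untouched, blood cortisol is one of many secondary predictors, and whether its level is associated with re-attempt can still be tested.

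**What to change.** - **Discussion, cortisol paragraph:** describe the measure as *fasting morning cortisol after the attempt*, neither as acute stress provoked by the attempt nor as basal cortisol. State that no conclusion about acute HPA reactivity will be drawn from it.
- **Analysis of blood cortisol:** as a sensitivity analysis, adjust the comparison for hours from attempt to draw (from admission where the attempt time is unknown), derived from chart and laboratory times where these are recorded. Repeat it in patients sampled on the first morning, leaving out rescheduled draws.

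The cost is a narrower claim, one derived variable with one degree of freedom, and a little extra analysis. No new sampling is needed.

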#### Secondary Outcomes

Chi-squared (χ2) tests will be used to assess the relationship between re-attempts and qualitative variables; independent *t*-test and Mann-Whitney will be used to compare parametric and non-parametric variables between the two groups of re-attempts and no re-attempts. Variables with a *P*-value lower than 0.2 will be included in a multiple Cox regression model to estimate the adjusted hazard ratio (AOR) with a 95% confidence interval (CI) for the risk factors associated with re-attempt suicide. In all the tests, the confidence interval will be 95%, and *P* < 0.05 to be considered significant.

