## Discussion

The main purpose of the SURAYA study is to assess the incidence of suicide re-attempt after a first attempt in a cohort of young people aged 16 to 25. The study's main strength is the homogeneity of participants: a narrow age group relevant to a critical period of neurodevelopment, and an incipient cohort in terms of onset of suicidal behaviors. There is little research focusing on suicidal behaviors in adolescents and young adults, and we do not currently know whether this group is at a higher risk of early suicide re-attempt compared to a general adult population.

Taken separately, most suicide risk factors previously identified are reported to be weak predictors of later suicidal ideation and behavior. In order to gain a comprehensive view of the potential prognostic factors of suicide re-attempts, we carefully collected a wide range of socio-demographic, clinical, and biological data relevant to suicidality; we used both self- and clinician-administered validated scales for more reliability across psychometric evaluations. We emphasized on emerging psychiatric disorders, addictions, psychotrauma, impulsivity and anger, environmental triggering factors, and severity of the first suicide attempt with the C-SSRS.

Beyond these features, we chose to include participants regardless of their psychiatric diagnosis, to capture transnosographic correlates of suicide re-attempts, and thus minimize the effect of potential confounding factors of comorbid psychiatric disorders. However, ICD10 diagnostic criteria will be included in the analysis of conditions such as depression or borderline personality disorder being particularly prevalent in the included population. Attenuated psychotic symptoms (i.e., ultra-high risk population), measured by the PQ-B, are also an interesting symptomatic dimension, as the onset of the disorder can frequently be manifested by an act of aggression. A recent meta-analysis of suicide risk during this time period suggests that suicidal and self-harming thoughts and behaviors were highly prevalent in the ultra-high risk population (40).

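### Depression is named as a confounder of cortisol, but the only stated rule for entering covariates leaves adjustment for it to a univariate P<0.2 screen

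*Protocol article*

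**What the plan says.** Two places in the Discussion state an intention about depression. On cortisol, the article says that "depression is a potential confounding variable of cortisol measures and will be considered in the analysis". Earlier, after explaining that participants are included whatever their diagnosis, it adds that "ICD10 diagnostic criteria will be included in the analysis of conditions such as depression or borderline personality disorder". Neither sentence says how this will be done.

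The method is under Statistical Analysis, Secondary Outcomes. Chi-squared "tests will be used to assess the relationship between re-attempts and qualitative variables"; the t-test and Mann-Whitney test "will be used to compare parametric and non-parametric variables between the two groups of re-attempts and no re-attempts". Then: "Variables with a *P*-value lower than 0.2 will be included in a multiple Cox regression model". No variable is named as always included, and no separate depression-adjusted cortisol model is described.

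Depression severity is measured at baseline with the QIDS-SR16 (Psychometric Measures and Clinical Factors). Age and gender are also recorded (Socio-Demographic Factors).

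**The concern.** A confounder of a cortisol effect is related both to cortisol and to re-attempt. The stated screen looks only at the second relation, and judges it by a P-value that depends on the number of events as well as on the strength of the association. With few events, a real but modest association often fails to reach P<0.2. Depression would then be left out of the model in which the cortisol hazard ratio is estimated, although the Discussion says it will be taken into account.

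At stake is whether a cortisol association with re-attempt can be reported as adjusted for depression. Under the rule as written, that is known only once the data have been tested.

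**Working it through.** The protocol gives no figure for how the screen performs, so there is none to reproduce. Its one sample-size figure, the precision of the incidence estimate, does not bear on this point.

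**Inputs from the protocol.** n = 200 and an expected 3-month re-attempt rate of 12.4% (Sample Size Calculation): 200 × 0.124 = 24.8, about 25 events and 175 non-events. Preliminary rate 17.81% in the first 73 patients (Trial Status): 200 × 0.1781 = 35.6, about 36 and 164. Screening threshold: two-sided P<0.2, critical z = 1.2816.

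**Assumed, because the protocol does not give them.** The true difference in depression score between groups (0.2, 0.3 or 0.5 SD), the prevalence and odds ratio of a depression diagnosis, and the correlation of depression with cortisol.

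**1. Continuous depression score, normal approximation.** SE of the standardised difference = sqrt(1/n1 + 1/n0), and P(fail) = Φ(1.2816 − d/SE) − Φ(−1.2816 − d/SE).

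- 25 v 175: SE = sqrt(1/25 + 1/175) = 0.2138. For d = 0.2, 0.3, 0.5, d/SE = 0.935, 1.403, 2.338, and P(fail) = 62%, 45%, 15% (rounded).
- 36 v 164: SE = sqrt(1/36 + 1/164) = 0.1841. For the same d, d/SE = 1.09, 1.63, 2.72, and P(fail) = 57%, 36%, 8%.

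**2. Depression as a yes/no diagnosis.** Probability of failing the chi-squared screen, from 20,000 simulated trials of 200 per scenario, at an assumed prevalence of 50%:

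| True odds ratio | 12.4% events, without / with Yates | 17.81% events, without / with Yates |
|---|---|---|
| 1.5 | 62% / 71% | 57% / 64% |
| 2 | 38% / 46% | 29% / 35% |
| 3 | 12% / 17% | 6% / 8% |

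Across prevalences of 30% to 70% at 12.4% events, an odds ratio of 1.5 fails in 62–67% without Yates (71–76% with), and an odds ratio of 2 in 38–47% (46–58% with).

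**3. What failing the screen does to the cortisol estimate.** Simulation with 200 patients, 12.4% events, a true cortisol effect of zero and 3,000 runs per scenario. A logistic model stands in for the Cox model, and cortisol is always kept in it. Entries are mean log-odds ratios per SD of cortisol:

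| Correlation, cortisol–depression | Depression OR per SD | Depression fails screen | Never adjusted | Always adjusted | Adjusted only if P<0.2 |
|---|---|---|---|---|---|
| 0.3 | 1.22 | 62% | 0.062 | 0.000 | 0.016 |
| 0.3 | 1.35 | 46% | 0.089 | −0.004 | 0.012 |
| 0.3 | 1.49 | 29% | 0.118 | −0.002 | 0.011 |
| 0.5 | 1.22 | 62% | 0.106 | 0.004 | 0.029 |
| 0.5 | 1.35 | 46% | 0.148 | −0.007 | 0.020 |
| 0.5 | 1.49 | 29% | 0.203 | 0.000 | 0.020 |

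The screen often drops depression, but mostly in samples where its observed association with re-attempt is weak. The average bias that remains is therefore about 0.01 to 0.03, against 0.06 to 0.20 if depression is never adjusted for.

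**The case against.** The strongest reply is that nothing is contradicted. The rule says that variables passing the screen will be included; it does not say that no other variable may be. Taking depression into account can sit beside it, and a condensed article may leave the mechanism to a fuller document. This stands in part: a reader might infer a flat contradiction, and the wording does not support one. It does not remove the point. The article does state an entry rule, and that rule alone does not secure the adjustment the article promises.

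The second reply is that failing a screen is not bias, and that the average bias is small. This stands. A reader might infer that the biological aims could not be interpreted, but the third calculation does not support that.

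The third reply concerns the width of the point. One might extend it to the method of the index attempt and the hours to sampling, since the Study Design says "Patients who are not fasting will be rescheduled". But sampling is otherwise standardised (fasting, 7:00 am, the morning after admission), the frequency of rescheduling is not given, and time of attempt is not listed among the data collected. The Discussion also treats blood cortisol as a measure of the stress that the attempt provokes, so adjusting for features of the attempt may remove part of what is being measured. One might also attack the Discussion's claim that inclusion across diagnoses will "thus minimize the effect of potential confounding factors of comorbid psychiatric disorders". The next sentence there says that diagnoses such as depression will enter the analysis, so the article does not rely on unrestricted inclusion alone. Neither extension is pressed here.

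**Conclusion.** The point holds in a limited form. The protocol names depression as a potential confounder of cortisol, and its only stated entry rule makes adjustment depend on a noisy test. For a depression score differing by 0.2 to 0.5 SD, the chance of missing the screen runs from 62% down to 15% at about 25 events, and from 57% down to 8% at about 36. Loss to follow-up was not allowed for in the sample size (Discussion), so events could be fewer.

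The failure rates rest on assumed effect sizes. It would be wrong to say in general that a moderate confounder is lost half the time: that is roughly true at 0.3 SD and 25 events, and not at 0.5 SD. The expected bias is small under the effects assumed, about 0.01 to 0.03 log-odds ratio per SD. The primary incidence estimate is untouched; the aims concerned are secondary and described as exploratory. The change is still worth making, because it is cheap and makes the Discussion's statement true.

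**What to change.** Add to Secondary Outcomes that any model estimating a blood or hair cortisol effect always contains depression severity (QIDS-SR16), age and sex, whatever their univariate P-values. Fit one biomarker at a time, and use a Firth-penalised Cox model if events are few. Naming the QIDS-SR16 also settles which depression variable is meant, since the article mentions both this score and clinical diagnoses. The P<0.2 screen may stay for the remaining, purely exploratory variables. Method of the index attempt, and time to sampling where it is recorded, belong at most in a sensitivity analysis.

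Cost: wording only, with no new data, visits or patients. Each cortisol model would have four coefficients (cortisol, depression, age as a linear term, sex), so 24.8/4 = 6.2 events per coefficient at the planned rate and 35.6/4 = 8.9 at the preliminary rate. That is thin, which is why one biomarker per model and the penalty are suggested. The price is a few degrees of freedom and slightly wider intervals.
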